### Sample size

Sample size was determined in relation to the planned analysis of primary outcomes (i.e. linear mixed models of anxiety/depression severity) and calculated in the R package ‘powerlmm’ [34]. Model parameters (random intercept/slope, residual variance) required for this calculation were estimated from similar data from a previous trial on a transdiagnostic intervention in primary care [26]. Given a 2:1 randomization ratio, longitudinal data collected at four timepoints across both groups, 30% research attrition at the primary endpoint and a moderate post-treatment between-group effect size of *d*=0.5 in line with previous research [21, 35], a sample size of 120 (iUP=80, WLC=40) was estimated to yield sufficient statistical power of 0.83 (a Bonferroni-adjusted *p* value of 0.025 to account for two primary outcome measure would reduce power to 0.75; at a lower attrition rate of 20% rather than 30%, power of 0.80 would be reached even with the Bonferroni-adjusted *p* value).

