### Randomization

Following the initial assessment and providing that the participant meets criteria for being included in the study, participants will be randomly allocated at an individual level using an algorithm developed by a computer scientist [41] and executed independently of the research team, employing random permuted blocks using block sizes of 6, and including stratification within a 2:1 allocation ratio between treatment and waiting list control groups. Post assessment, the clinician/researcher administering the M.I.N.I. opens concealed allocation and will then inform the participant of their allocation into either the wait-list or treatment group. The clinicians/supporters carried out the support of the clients in the intervention could not be blinded to allocation for practical reasons; however, the clinicians/researchers conducting the pre-trial assessment are going to be blind to the condition allocation during the assessment.

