### Data analysis

All the analyses will follow the intention-to-treat principle and reporting of the results will adhere to CONSORT recommendations. Missing data analysis will explore missing data patterns and mechanisms. Multiple imputation will be considered where deemed necessary. Linear mixed models will be used to evaluate primary and secondary outcomes. In these models, intercepts and/or slopes will be allowed to vary on the level of the individual where appropriate and time and treatment group as well as their interaction will be included as fixed effects. To allow for the nesting and comparing of models in terms of model fit, models will be estimated via maximum likelihood estimation during model building. Final models will utilize restricted maximum likelihood estimation. Separate linear mixed models utilizing only data from the iUP group will be built to assess the maintenance of effects into follow-up, including random intercepts/slopes and time as a fixed effect. Between-group Cohen’s *d* effect sizes will be calculated based on raw standard deviations [52]. The qualitative data will be analysed using a descriptive-interpretive approach [53].

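### Randomisation is said to be stratified, but the fixed effects listed for the mixed models include no stratification factor; the likely cost is slight conservatism of unknown, probably small, size

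*Protocol article*

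**What the plan says.** The Randomization section of the protocol article describes allocation of individuals "employing random permuted blocks using block sizes of 6", "including stratification within a 2:1 allocation ratio between treatment and waiting list control groups". No stratification factor and no number of strata is given there or elsewhere in the article.

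The Data analysis section assigns linear mixed models to the primary and secondary outcomes. Of the fixed part it says that "time and treatment group as well as their interaction will be included as fixed effects"; of the random part, that "intercepts and/or slopes will be allowed to vary on the level of the individual where appropriate". It lists no stratification factor or other baseline covariate. It also describes a model-building stage in which nested models are compared for fit.

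The Sample size section reports that "a sample size of 120 (iUP=80, WLC=40) was estimated to yield sufficient statistical power of 0.83", assuming "a moderate post-treatment between-group effect size of *d*=0.5" and "30% research attrition at the primary endpoint". A Bonferroni level of 0.025 "would reduce power to 0.75". Stratification is not mentioned in that calculation.

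**The concern.** Blocking within strata forces the arms to be balanced on the stratification factor. If the factor predicts the outcome, the true sampling variance of the treatment contrast falls. A model without the factor still counts the between-stratum variation as error, so its standard errors are larger than the real variability of the estimate. Confidence intervals are then somewhat too wide and the test rejects less often than its nominal level.

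What is at stake is efficiency: part of the gain that stratification was meant to bring is not realised. There is also a smaller matter of pre-specification. The article describes choosing among models by fit and gives no rule for the strata, so whether they enter could be decided after the data are seen.

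**Working it through.** **1. The plan's own figure.** The power of 0.83 cannot be rebuilt, because the variance components taken from an earlier trial are not given. Its consistency with the other stated figures can be checked. Assume a two-sided 0.05 level, inferred from 0.025 being the Bonferroni value for two outcomes.
- Implied noncentrality: 1.960 + 0.954 = 2.914.
- At 0.025: Φ(2.914 − 2.241) = 0.749 (stated 0.75).
- At 0.025 with 20% attrition: 2.914 × √(0.8/0.7) = 3.115, and Φ(3.115 − 2.241) = 0.809 (stated 0.80).

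The three figures agree with one another, so 2.914 is used below.

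**2. Formulas.** Let R² be the share of the variance of the analysed contrast that the strata explain. Under stratified allocation with the strata left out of the model:
- Standard error overstated by the factor f = 1/√(1 − R²).
- True size of the 5% test: 2 × (1 − Φ(1.960 f)).
- Actual power without the strata: Φ(0.954 f).
- Power with the strata fitted: Φ(2.914 f − 1.960).

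**3. Group-by-time effect, generalised least squares.** Assumed components, chosen to reproduce 0.83: intercept variance 0.7, residual variance 0.3 (baseline SD 1), slope variance 0.007. There are four visits coded 0 to 3, d = 0.5 at the last, 80:40 allocation, and monotone dropout reaching 30%. The stratum has two levels.

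| Share of baseline variance explained by stratum | Stratum omitted | Stratum main effect | Plus stratum by time, same share of slope variance |
|---|---|---|---|
| 5% | 0.830 | 0.830 | 0.832 |
| 10% | 0.830 | 0.831 | 0.835 |
| 20% | 0.830 | 0.832 | 0.840 |

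These powers use model-based standard errors. The gain is at most about 0.2 points with a main effect and about 1 point with the time interaction added.

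**4. Why the effect is small.** A constant difference between strata is absorbed by the random intercept and largely cancels from change over time. Only slope variance is left for the strata to explain. With complete data, the squared deviations of 0 to 3 from their mean sum to 5. The variance of one participant's fitted slope is therefore 0.007 + 0.3/5 = 0.067, and slope variance is 0.007/0.067 = 10.4% of it.
- A factor explaining 20% of slope variance gives R² = 0.20 × 10.4% = 2.1%. Then f = 1.011, true size is 4.8%, and power is 0.833 without and 0.838 with the strata, a gain of about 0.5 points.
- A factor explaining all slope variance gives R² = 10.4%. Then f = 1.057, true size is 3.8%, and power is 0.843 without and 0.869 with the strata, a gain of about 2.5 points. This is the ceiling under these components.

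**5. A less favourable contrast.** This is a comparison at a single visit with no use of baseline, which is not the stated analysis. Fix power at 0.83 with the strata fitted. Power without them is Φ(2.914 − 1.960 f). For R² of 2%, 5%, 10% and 20% this is 0.825, 0.817, 0.802 and 0.765, with standard errors too large by 1%, 3%, 5% and 12%.

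**6. Simulation under no effect.** Permuted blocks of 6 were used within two strata, the stratum carrying about 9% of baseline variance, with REML fits and 245 runs. The mean standard error was 0.2295 and the rejection rate 4.9%, both with and without the stratum. This covered a main effect only, the number of runs is small, and some fits gave convergence warnings. It supports the main-effect result in step 3 and says nothing about a factor that predicts change.

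**The case against.** The strongest reply is that the article states which terms will be included and does not call the list exhaustive. It condenses a fuller protocol, and an unseen analysis plan may add covariates. A reader might infer that the model contains only those three terms, but the text does not say so. What stands against the reply is that the fixed part is stated positively, without the hedging applied to the random part, and that a stratified design is described alongside it. Saying whether the strata enter the model would close the gap.

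A reader might also infer a material loss of precision. If strata explained 5%, 10% or 20% of the variance of change, the step 2 formulas give true sizes of 4.4%, 3.9% and 2.8%, and power of 0.85, 0.87 and 0.90 with the strata fitted. The documents do not support that reading. The factor is unnamed and nothing in them supports those shares. Under the assumed components 20% is out of reach, and 5% would need about half of all slope variance. Even taking the shares as given, the trial without the strata in the model would have power of 0.836, 0.843 and 0.857, so the gain from fitting them is about 1, 2 and 5 points, not the full distance from 0.83.

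Nor is this a threat to validity: the error runs in the conservative direction.

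Finally, interactions of strata with time in every model would be costly if there were many strata, with about 84 participants (120 × 0.7) expected at the endpoint. That objection stands and limits the fix.

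**Conclusion.** The mismatch is real: the article says randomisation is stratified, and its listed fixed effects do not include the factor. If the factor is prognostic, particularly for change over time, the consequence is standard errors somewhat too large and a slightly conservative test. The size is unknown and probably small: about 0 to 1 power points for the group-by-time effect, and more only if the factor strongly predicts change. This estimate rests on assumed variance components, a two-level factor, a two-sided 0.05 level and monotone dropout, none of which the article gives in full. Confidence is high in the mismatch and low in any particular magnitude. The case for acting is that the change is nearly free and settles the model in advance.

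**What to change.** In Randomization, name the stratification factor or factors and their levels. In Data analysis, state that these factors enter all primary and secondary mixed models as pre-specified fixed effects, outside the model-fit comparisons. Where the number of strata is small, add their interaction with time, since a main effect alone barely affects a contrast of change. With many strata, keep to main effects.

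The cost is one sentence in each section and a few degrees of freedom. Factors used for allocation should already be on record, so no new data should be needed.

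If the word stratification was meant to describe only the blocking in a 2:1 ratio, correct the Randomization sentence to say so; the model then needs no change on this account.

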## Measures

### Diagnostic measure

#### The Mini-International Neuropsychiatric Interview (M.I.N.I. [39])

The M.I.N.I. is a brief structured psychiatric interview, which was designed as a diagnostic tool to identify the most common diagnosis in the DSM-5 [42] and ICD-10 [43]. The M.I.N.I. can be administered in as little as 15 min (mean 18.7 ± 11.6 min, median 15 min) and has similar reliability and validity to similar longer instruments. Clinicians/researchers administering the M.I.N.I will undergo a specific training programme prior to using the tool to ensure the quality standard is maintained. All clinicians administering the M.I.N.I will receive a training in the use of this tool.

### Primary outcomes measures

#### The Overall Anxiety Severity And Impairment Scale (OASIS, [32])

The OASIS is a 5-item measure that can be used to assess the impairment and severity which is associated with multiple anxiety disorders. Items are rated from 0 to 4 and summed to determine the overall score. A score of 8 or above is indicative of a probable anxiety disorder. The OASIS shows good psychometric qualities [38].

#### The Overall Depression Severity and Impairment Scale ODSIS (ODSIS***;*** [33])

The ODSIS is a 5-item self-report measure that can be used to assess severity and impairment with any depressive symptoms. Items are rated from 0 to 4 and summed to determine the overall score. A score of 8 or above is indicative of a probable depressive disorder. The ODSIS shows good psychometric qualities [33].

### Secondary outcome measures

#### Work and Social Adjustment Scale (WSAS; [44])

The WSAS is a 5-item scale which assesses functional impairment in work and social areas. It is a self-report measure that has been utilized with patients with depression and anxiety in primary care contexts.

#### Generalized Anxiety Disorder-7 (GAD-7; [45])

The GAD-7 is based on the DSM-IV diagnostic criteria for GAD and measures both the symptoms and severity of anxiety. GAD-7 displays good internal validity and good convergent validity with other anxiety scales. GAD-7 is a 7-item self-report instrument routinely used in the Irish and UK public health primary care with a cut-off score 8 and higher [46].

#### Patient Health Questionnaire-9 (PHQ-9; [40])

The PHQ-9 is a 9-item self-report scale with sound psychometric qualities measuring the severity of depression. The measure has the cut-off total score ≥ 10 [46]. PHQ-9 is routinely used in the Irish and UK public health primary case and therefore will be used for all clients in this study too.

### Disorder-specific measures

In addition to primary and secondary measures, there will be additional disorder-specific measures applied to the client depending on their primary diagnosis according to M.I.N.I. For the purpose of the primary diagnosis of depression, PHQ-9 will be used. In case of generalized anxiety disorder, it will be GAD-7. The scales listed here will be applicable to other primary diagnoses such as panic disorder, social anxiety, OCD and PTSD.

#### Panic Disorder Severity Scale-Self Report (PDSS-SR; [47])

The PDSS-SR is a 7-item measure to assess both frequency and severity of panic disorder symptoms. The seven items are rated on a 5-point scale that ranges from 0 to 4. The PDSS-SR assesses impairment in functioning; avoidance of situations and physical sensations; and frequency of panic, distress during panic and panic-focused anticipatory anxiety. A score of 9 or above is indicative of caseness. The scale has sound psychometric qualities.

#### Social Phobia Inventory (SPIN; [48])

The SPIN is a 17-item self-report scale that assesses symptoms of social anxiety disorder (each item scores 0 to 4). SPIN assesses the domains of social anxiety and asks users to reflect on their experiences over the past week. The scores are totalled to gain a representation of symptom severity with the score 19 and above meeting the clinical caseness. The scale has sound psychometric qualities.

#### Obsessive-compulsive Inventory-Revised (OCI-R; [49])

The OCI-R is an 18-item self-report scale that assesses obsessive-compulsive disorder symptoms, each item is rated on a 5-point Likert scale (0–4) with the cut-off score being 21 and above. The scale shows good psychometric qualities.

#### PCL-5 ( [50])

This is a 20-item self-report measure assessing symptoms of posttraumatic stress disorder (PTSD) according to DSM-5. Each symptom is scored on a scale 0–4 with the score 31 and above being a clinical cut-off. It has appropriate psychometric qualities.

#### Client Change Interview Protocol (CCIP; [51])

A written questionnaire variant of CCIP will be used to obtain clients’ answers to open ended questions post-intervention such as: What changes, if any, have you noticed in yourself since the internet-based Unified Protocol intervention started? Has anything changed for the worse for you since the internet-based Unified Protocol intervention started? Is there anything that you wanted to change that has not since the internet-based Unified Protocol intervention started? Can you sum up what has been helpful about your internet-based Unified Protocol intervention? What kinds of things about the intervention have been hindering, unhelpful, negative or disappointing for you? Were there things in the intervention which were difficult or painful but still OK or perhaps helpful? What were they? Has anything been missing from your treatment?

#### Engagement and usage measures

Online metrics of use will allow the study to measure and report on participants’ adherence to treatment (use) versus non-adherence to treatment (non-use), which is recommended by the CONSORT E-HEALTH guidelines [30]. A summary of all measures and time points is in Table 2.

**Table 2 Tab2:** A description (SPIRIT diagram) of enrolment, intervention and assessment

	Study period							
	Enrolment	Allocation	Post-allocation					
Timepoint	***-t***_***1***_	0	***Both conditions***			***Follow-up iUP only***		
			Week 4	Week 8	Week 12	Week 16	Week 20	Week 24
**Enrolment:**								
**Eligibility screening**	X							
**Informed consent**	X							
**Baseline assessment**	X							
**Study suitability**	X							
**Allocation**		X						
**Interventions:**								
***iUP***			**x**	x	x			
***eWLC***						x	x	x
**Assessments:**								
***OASIS***	X		X	X	X	X	X	X
***ODSIS***	X		X	X	X	X	X	X
***M.I.N.I.***	X							
***PHQ-9***	X		x	x	x	x	X	X
***GAD-7***	X		X	X	X	X	X	X
***WSAS***	X		X	X	X	X	X	X
***Engagement and usage***	X							
***Primary diagnosis-specific measure***	X		x	x	X	X	X	X
***CCIP***					X			

SPIRIT diagram of enrolment, intervention and assessment. Legend: *CCIP* Client Change Interview Protocol, OASIS Overall Anxiety Severity and Impairment Scale, *ODSIS* Overall Depression Severity and Impairment Scale, *PHQ-9* Patient Health Questionnaire, *GAD-7* Generalized Disorder 7, *WSAS* Work and Social Adjustment Scale, *M.I.N.I.* Mini-International Neuropsychiatric Interview

### Data analysis

All the analyses will follow the intention-to-treat principle and reporting of the results will adhere to CONSORT recommendations. Missing data analysis will explore missing data patterns and mechanisms. Multiple imputation will be considered where deemed necessary. Linear mixed models will be used to evaluate primary and secondary outcomes. In these models, intercepts and/or slopes will be allowed to vary on the level of the individual where appropriate and time and treatment group as well as their interaction will be included as fixed effects. To allow for the nesting and comparing of models in terms of model fit, models will be estimated via maximum likelihood estimation during model building. Final models will utilize restricted maximum likelihood estimation. Separate linear mixed models utilizing only data from the iUP group will be built to assess the maintenance of effects into follow-up, including random intercepts/slopes and time as a fixed effect. Between-group Cohen’s *d* effect sizes will be calculated based on raw standard deviations [52]. The qualitative data will be analysed using a descriptive-interpretive approach [53].

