#### Intervention

##### Internet-based Unified Protocol (iUP)

The iUP is an eight-module online intervention that is based on the second edition of the UP [21, 36]. It includes the five core CBT modules in the UP that target neuroticism (i.e. negative affect and aversive reactivity to emotions) and subsequent emotion motivated avoidant coping [37]. See Table 1 for an overview of the modules. The programme is self-directed, so the client can proceed through the programme at their own pace. The recommended time to spend on a module is initially 1 week, but starting with module 3, and for the rest of the core modules in the UP (Table 1), the supporter (see below) may suggest extra time, 2 or more weeks. Supporters particularly recommend that participants spend 2–4 weeks on module 7 (Emotion Exposures). Specific recommendations from supporters will also consider participant pace, progress and engagement with the programme (e.g. if someone does not complete a specific module 1 week, they may be encouraged to complete it the following week). This intervention will be delivered on the SilverCloud platform. SilverCloud Health is a global leader in the development of computerized psychological interventions for depression, anxiety, stress and comorbid long-term conditions. The intervention will be delivered on a Web 2.0 platform using media-rich interactive content. Consistent with other SilverCloud programmes, each module follows a structured format and includes videos, a psychoeducational content, interactive activities and tools, instructions for practicing skills and summaries of the modules. Clients’ progress and use of the iUP will be reviewed by a supporter, who will provide feedback on the client’s use of the programme. Their support will consist of email messages to the clients that provide encouragement and suggestions for the use of the programme. The feedback will be provided every 6 to 10 days. The supporters will be assistant psychologists and/or trainee psychologists. They will be under supervision of a qualified psychologist. All participating clinicians will be trained by an UP trainer in the delivery of support for iUP and in addition will receive training on the platform and how to deliver supporter reviews to participants.

**Table 1 Tab1:** Modules in the Internet-based UP

Module name	Brief description

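### Only iUP clients have a supporter, yet the power calculation and the mixed models name only individual-level variation, so the stated power of 0.83 assumes zero supporter clustering and is an upper bound

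*Protocol article*

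**What the plan says.** **Supporters (Internet-based Unified Protocol section).** A client's progress "will be reviewed by a supporter, who will provide feedback on the" way the programme is used, at intervals of 6 to 10 days. From the third module on, "the supporter (see below) may suggest extra time, 2 or more weeks". Supporters are assistant or trainee psychologists. Neither their number nor their caseload is given, and nothing says that a client keeps the same supporter.

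**Control arm (Enhanced Wait-List Control section).** Clients take up the listed resources at their own initiative. They have no supporter.

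**Power (Sample size section).** "Model parameters (random intercept/slope, residual variance) required for this calculation were estimated from similar data" in a previous trial. With 80 iUP and 40 control clients, four timepoints, 30% attrition and d = 0.5, the sample "was estimated to yield sufficient statistical power of 0.83". For the stricter test, "a Bonferroni-adjusted *p* value of 0.025 to account for two primary outcome measure would reduce power to 0.75". No supporter-level variance, ICC or design effect is mentioned.

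**Model (Data analysis section).** Time, group and their interaction are fixed effects, and "intercepts and/or slopes will be allowed to vary on the level of the individual where appropriate". No supporter level is named.

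**The concern.** Clients are randomised individually, but the arms differ in structure. In the iUP arm, clients who share a supporter share that person's feedback style and advice on pace, so their outcomes may be correlated. In the control arm nothing comparable exists, apart from an optional single consultation in an advice clinic. This is a partially nested design.

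A random intercept and slope per person deals with repeated measures on that person. It does not deal with correlation between people who share a supporter. If supporters differ in the change they produce, the variance of the mean change in the iUP arm is larger than the model assumes. The standard error of the time-by-group contrast on OASIS and ODSIS is then too small, and an analysis with the correct standard error has less power than the figure used to justify N = 120.

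**Working it through.** **Inputs from the protocol article.** 80 iUP and 40 control clients; 30% attrition, leaving 80 × 0.7 = 56 and 40 × 0.7 = 28; d = 0.5; power 0.83, or 0.75 at the 0.025 level. Two-sided 5% for the 0.83 is inferred from the Bonferroni value of 0.025 for two outcomes.

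**Assumed, because not given.** ICC for change to week 12: 0.01 to 0.05. Number of supporters k: 4 to 12. Caseloads equal, and one supporter per client throughout.

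**Step 1: the plan's own figure.** The variance components are not printed, so 0.83 cannot be recomputed directly. A plain two-group comparison of 28 with 56 at d = 0.5 has power 0.58. An effective baseline-to-endpoint correlation of about 0.67 would raise that to 0.83, which is plausible for a longitudinal model. The stated figures also agree with each other. Power 0.83 implies a non-centrality of 1.960 + 0.954 = 2.914. At the 0.025 level this gives 0.749 (stated 0.75). With 20% attrition, 2.914 × √(0.8/0.7) gives 0.809 (stated 0.80). On its independence assumption, 0.83 is not contradicted.

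**Step 2: clustering in the iUP arm only.**
- Caseload m = 56/k; design effect DE = 1 + (m − 1) × ICC.
- Variance ratio = (1/28 + DE/56) / (1/28 + 1/56) = (2 + DE)/3. The SE ratio R is its square root.
- Power with the correct SE = Φ(2.914/R − 1.96).
- False-positive rate if clustering is ignored = 2 × [1 − Φ(1.96/R)].

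Example, k = 4 and ICC 0.05: m = 14; DE = 1 + 13 × 0.05 = 1.65; R = √(3.65/3) = 1.103; power = Φ(2.642 − 1.96) = 0.752; false-positive rate = 2 × [1 − Φ(1.777)] = 7.6%.

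| ICC | k | DE | R | Power | False-positive rate |
|---|---|---|---|---|---|
| 0.01 | 4 | 1.130 | 1.021 | 0.814 | 5.5% |
| 0.01 | 8 | 1.060 | 1.010 | 0.823 | 5.2% |
| 0.01 | 12 | 1.037 | 1.006 | 0.825 | 5.1% |
| 0.05 | 4 | 1.650 | 1.103 | 0.752 | 7.6% |
| 0.05 | 6 | 1.417 | 1.067 | 0.780 | 6.6% |
| 0.05 | 8 | 1.300 | 1.049 | 0.793 | 6.2% |
| 0.05 | 12 | 1.183 | 1.030 | 0.808 | 5.7% |

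If caseloads are based on the 80 randomised instead (m = 20 for four supporters), power at ICC 0.05 is 0.72 rather than 0.75. At the 0.025 level, the stated 0.75 becomes 0.66 with four supporters and 0.70 with eight (ICC 0.05, m = 56/k).

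**Step 3: degrees of freedom.** The normal approximation ignores how few supporters there may be. With v₁ = DE/56 and v₂ = 1/28, the Satterthwaite degrees of freedom are (v₁ + v₂)² / [v₁²/(k − 1) + v₂²/27]. At ICC 0.05 this gives 12.6 for k = 4 and 28.0 for k = 8, and non-central t power of about 0.68 and 0.77. Part of that loss is the price of estimating a supporter variance at all: at ICC 0 with four supporters, the degrees of freedom alone take 0.83 to about 0.79.

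All of this is a two-group analogue of the planned four-timepoint model. It shows the order of magnitude, not the exact result.

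**The case against.** **The ICC may be small.** The programme is self-directed with fixed online content, and support consists of email messages from trained and supervised staff. That leaves less room for supporters to differ than face-to-face therapy does. This stands: at ICC 0.01 the normal-approximation loss is about 0.5 to 2 points with 4 to 12 supporters.

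**Shared caseloads are not stated.** That is so, but 80 iUP clients in one Dublin-based service make one supporter per client implausible. It is a strong inference, and should be read as one.

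**The false-positive figures need a particular null.** If iUP changed nobody's outcome, supporters could not differ in effect and individual randomisation would protect the test. Inflation requires supporter effects that vary around an average of zero, and inference to supporters beyond those in the trial. For a trial that calls itself exploratory, conclusions conditional on these supporters are defensible. This stands as a limit on those figures.

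**The analysis plan may add the term.** The article condenses a fuller plan and does not exclude a supporter effect. But it does fix the level at which random effects vary, and prints a power figure on matching inputs. A term added later would not change what the 0.83 assumes.

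**Stronger reading.** A reader might infer that 0.83 is wrong, or that the trial is underpowered. The documents do not support that: the printed powers are mutually consistent, and no ICC or supporter count is given from which a shortfall could be shown.

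**Conclusion.** The point holds in structure and direction; its size is open. Only the iUP arm is nested in supporters, and both the power calculation and the models are described with individual-level variation alone. The 0.83 is therefore reached only at a supporter ICC of zero, and any positive ICC makes the planned standard error too small.

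By normal approximation with 56 and 28 analysed and 4 to 12 supporters, power is about 0.81 to 0.83 at ICC 0.01 and 0.75 to 0.81 at ICC 0.05. With small-sample degrees of freedom it is about 0.68 (four supporters) and 0.77 (eight) at ICC 0.05. The nominal 5% test would reject in about 5.1% to 5.5% of trials at ICC 0.01 and 5.7% to 7.6% at ICC 0.05, under a null in which supporter effects vary around zero. The ICC and supporter numbers are assumptions, so the consequence runs from negligible to moderate.

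**What to change.** 1. **Record the supporter.** Hold a coded supporter identifier for each iUP client, and any change of supporter. Do this before anonymisation: the Data management section says the data will be fully anonymised once collected, after which an unrecorded link may be lost.
2. **Pre-specify a partially nested analysis of OASIS and ODSIS.** Add a supporter-level random slope that applies in the iUP arm only, treat each control client as a unit of their own, and use Satterthwaite or Kenward-Roger degrees of freedom. Make this at least a sensitivity analysis. Whether it should be the primary model is debatable if supporters are few. If clients change supporter, a multiple-membership structure is needed.
3. **Qualify the power statement.** Say in the Sample size section that 0.83 assumes no supporter clustering. Give power over a range of ICCs for the expected number of supporters, calculated with the same degrees-of-freedom method as the analysis.

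N need not change. The cost is one identifier, one variance term and a lower stated power. Confidence intervals from the nested model will be somewhat wider, and the supporter variance will be imprecise if there are few supporters.
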